##### Quality of Life (World Health Organization Quality of Life-Bref)

 The World Health Organization Quality of Life-Bref [41] is a 26-item multidimensional measure of quality of life that assesses subjective quality of life. This instrument measures four dimensions of quality of life (physical, psychological, social relations, and environment). It can also be used as a measure of general quality of life.

### Secondary Outcomes

#### Psychological (In)flexibility (Comprehensive Assessment of ACT)

 The Comprehensive Assessment of ACT [42,43] is a measure of psychological flexibility as conceptualized by ACT, with three subscales: openness to experience, valued action, and behavioral awareness. This project will use the short version with 18 items, measured in a Likert-like 7-point scale (0–“Strongly disagree” to 6–“Strongly agree”).

#### Emotional (Dys)regulation (Difficulties in Emotion Regulation Scale-Short Form)

 The Difficulties in Emotion Regulation Scale-Short Form (DERS-SF) [44,45] is an 18-item version of the DERS scale that assesses difficulties in regulating emotions in 6 different dimensions, 3 items per dimension, measured in a 5-point Likert scale (1=almost never to 5=almost always): nonacceptance of emotional responses, (2) difficulties engaging in goal-directed behavior, (3) impulse control difficulties, (4) lack of emotional awareness, (5) limited access to emotion regulation strategies, and (6) lack of emotional clarity. This scale can be used unidimensionally to measure difficulties in emotional regulation, where higher scores mean more difficulties in emotional regulation.

#### Mindful Awareness (Mindful Attention Awareness Scale)

 The Mindful Attention Awareness Scale [46,47] is a 15-item scale designed to assess a core characteristic of mindfulness, namely, a receptive state of mind in which attention, informed by a sensitive awareness of what is occurring in the present, simply observes what is taking place. It measures mindful awareness in a 6-point Likert-like scale (1=almost always; 6=almost never).

#### The Triple Network

 The functional connectivity of the Triple Network will be assessed through fMRI, specifically examining the functional connectivity of brain regions involved in chronic pain, including brain networks related to self-reflection (DMN), emotion (SN), and cognitive control (FPN).

#### System Usability Scale

 The System Usability Scale [46,47] is a 10-item scale that measures global view system usability (example item: “I thought the system was easy to use”), through a 5-point response scale ranging from 1=strongly disagree to 5=strongly agree.

### Data Analyses: Feasibility and Preliminary Efficacy

The feasibility of VR-ACT will be assessed qualitatively through open-ended questions (eg, “What would you say were the benefits of using the VR-ACT headset?,” “What have you learned from the VR-ACT program?”) designed to explore adherence, engagement, and acceptability of the intervention (see Section A in Multimedia Appendix 1). Thematic analyses will be conducted with the support of NVivo, and common themes in each question will be categorized. Also, feasibility will be quantitatively assessed through (1) dropout rate, (2) number of usage of the VR headset (embedded software usage monitoring), (3) percentage of intervention completion, (4) a 5-point Likert scale measuring usefulness, comprehensibility, and likelihood to continue using learned skills. The usability of the VR-ACT will be quantitatively assessed through the System Usability Scale.

The preliminary efficacy of VR-ACT will be pilot tested through 2 statistical methods: (1) intention to treat analyses, using linear mixed models to examine statistically significant change over time, moderated by allocation, and post hoc differences, adjusted for multiple comparisons using the Bonferroni technique; (2) reliable change index for each outcome for preintervention to postintervention timepoints, to assess clinically significant individual changes [48]. Network-based statistics [49] will be used to assess significant differences in network connectivity within and between conditions.

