#### Sample Size Calculation

 The study was powered for a large final timepoint between-group effect size (standardized mean difference=0.8), allowing for a variant autoregressive ρ over 2 measurements (preintervention and postintervention; 1 and 0.8) to accommodate the likely instability of the outcome variable(s). Setting the α at .05 and a minimum of 80% power, a minimum sample size of N=30 is required (EC: n=15; CC: n=15). We used the power.mrmm function from the R “longpower” package, through WebPower. A sample size of 15 to 30 participants is also sufficient to attain saturation in qualitative analyses conducted through interviews [32].

 To minimize dropout, (1) 2 phone calls will occur during the VR-ACT implementation to address questions on the VR-ACT content. (2) We also expect minor technical difficulties when using the VR headset. At the beginning of each module, an avatar therapist will provide a welcome message, reminding you of the research team’s contact information in case of any technical problems. Before the implementation, an online group meeting will be conducted to introduce the VR headset to participants in both conditions and help with navigation. (3) To promote engagement, weekly emails will be sent to all participants reminding them to use the VR headsets. Also, after the VR system registers 3 days of absence, automatic reminders will be sent to the participants' emails.

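### The time-by-allocation efficacy test is valid, but adjusting for the pre-randomisation baseline would estimate the same between-arm difference more precisely

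*Protocol article*

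**What the plan says.** The section Data Analyses: Feasibility and Preliminary Efficacy plans an intention-to-treat analysis "using linear mixed models to examine statistically significant change over time, moderated by allocation, and post hoc differences", with Bonferroni adjustment, and a reliable change index for individual change. It does not say whether the T0 means are left free or held common to both arms, and it does not define the post hoc contrasts. For the fMRI outcome, network-based statistics "will be used to assess significant differences in network connectivity within and between conditions".

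The Data Collection section places the T0 questionnaires and the first fMRI before random assignment, with one later assessment, T1. The Sample Size Calculation section takes a "large final timepoint between-group effect size (standardized mean difference=0.8"), "allowing for a variant autoregressive ρ over 2 measurements (preintervention and postintervention; 1 and 0.8"), and 15 participants per arm. The Discussion states the efficacy hypothesis as superiority of VR-ACT over Sham VR.

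**The concern.** Change over time moderated by allocation is the time-by-allocation interaction. With two timepoints and free baseline means, that interaction is the difference between arms in mean change. Subtracting T0 in full corrects for baseline with a slope of 1, whereas the best slope under equal variances is ρ. Unless ρ is close to 1, the subtraction adds noise that baseline adjustment would avoid. Randomisation after T0 makes the adjustment legitimate, and the T0 data are collected anyway. In a trial of 30 this affects the width of every interval, and the article intends the results as a reference point for a larger trial.

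A smaller matter is the within-condition testing of connectivity. Such tests do not address superiority over sham. A significant change in one arm beside a non-significant change in the other is not evidence of a difference between the arms.

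**Working it through.** **Inputs.** Standardised difference 0.8, 15 per arm and α = .05 come from Sample Size Calculation. Two-sided testing is assumed because sidedness is not stated. ρ is the T0-T1 correlation. The section prints 1 and 0.8 for its two measurements; 0.8 may be a correlation, but it could also be read as 80% retention. I therefore show ρ = 0.5 and 0.6 as assumptions next to 0.8. Further assumptions are equal SDs at T0 and T1, no dropout, and one outcome tested at the full α.

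**The plan's own figure.** A plain T1 comparison needs n per arm = 2 × ((1.96 + 0.842)/0.8)² = 24.5, so 25 (N = 50). The stated N = 30 is not reproduced this way. At 15 per arm that comparison has about 56% power (noncentral t). A change-score contrast would need 15 per arm at ρ of about 0.69, which is not stated. How N = 30 was reached is a separate question; here 15 per arm is taken as given.

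**Same target.** Because T0 precedes randomisation, the expected T0 difference between arms is zero. The expected difference in change therefore equals the expected difference at T1. The two estimators differ only in variance.

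**Variance factors, in units of σ² per participant.**
- Change score: Var(T1 - T0) = 2(1-ρ).
- Baseline-adjusted: 1-ρ².
- Ratio, adjusted to change: (1-ρ²)/(2(1-ρ)) = (1+ρ)/2.

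The ratio is 0.75, 0.80 and 0.90 at ρ = 0.5, 0.6 and 0.8. Estimating the baseline slope at N = 30 has a cost: the adjusted variance is multiplied by 1 + 1/26, and 27 rather than 28 degrees of freedom remain. The ratios become 0.779, 0.831 and 0.935.

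**Power.** Noncentrality is 0.8/√(2φ/15), where φ is the variance factor.

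| ρ | φ, change | φ, adjusted (× 27/26) | Power, change | Power, adjusted |
|---|---|---|---|---|
| 0.5 | 1.00 | 0.779 | 56.2% | 66.8% |
| 0.6 | 0.80 | 0.665 | 65.7% | 73.6% |
| 0.8 | 0.40 | 0.374 | 91.7% | 93.2% |

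The gain is about 11, 8 and 2 percentage points (1.5 before rounding at ρ = 0.8).

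**Within-condition tests.** Suppose both arms improve equally and each pre-post test has 50% power. Then the pattern of VR-ACT significant and sham not arises with probability 0.5 × 0.5 = 25%, although the arms do not differ. In a simulation with 15 per arm, equal improvement of 0.3 to 0.5 SD and ρ of 0.5 or 0.8, the pattern occurred in 15% to 25% of runs, and in 11% to 22% with Bonferroni over two tests. These figures matter only if a reader treats the pattern as evidence of efficacy.

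**The case against.** The strongest reply is that nothing here is invalid. Time by allocation is a between-arm contrast protected by randomisation. A linear mixed model can also hold the T0 mean common to both arms, in which case the plan already does what is recommended. The article is condensed and no analysis plan is shown. This stands in part: the text does not rule out a constrained baseline, so the point is an improvement to state, not an error to correct.

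The gain also depends on ρ. At 0.8, the only candidate value printed, it is under 2 points. Adding further covariates without prognostic value could use it up: a simulation that also adjusted for age and wave gave 91.8% at ρ = 0.8, against 91.7% for the change score. This stands too. However, the same section cites likely instability of the outcomes as a reason for its assumptions, so a high correlation should not be relied on.

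Two stronger readings are tempting. A reader might infer that the sample size targets a different quantity from the analysis, since it speaks of a final-timepoint difference. It does not: with T0 before randomisation, both contrasts have the same expected value. A reader might also infer that within-arm significance is the planned evidence of efficacy. The document does not say so. Explicit within-condition testing is confined to connectivity, a secondary outcome, and sits beside a between-condition test. The post hoc contrasts are undefined and may be between-arm. No section treats significance in one arm only as efficacy.

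**Conclusion.** The concern holds as a matter of precision and clarity. The planned interaction test is valid. Fitted in the usual way, with free baseline means, it is less precise than a baseline-adjusted estimate of the same difference. After the small-sample cost, adjustment cuts the variance by about 22% at ρ = 0.5, 17% at 0.6 and 6.5% at 0.8, worth about 11, 8 and 2 points of power respectively. These sizes rest on equal SDs, complete data and two-sided testing, and the two larger gains rest on assumed correlations.

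For connectivity, within-condition results cannot support the superiority hypothesis, and labelling them descriptive would prevent misreading.

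**What to change.** In Data Analyses, state the efficacy estimate for each outcome as the VR-ACT minus sham difference at T1, from a mixed model with a common T0 mean or from ANCOVA on T0, with a 95% CI. The mixed model suits the intention-to-treat aim because it keeps participants who have T0 data only. If a common T0 mean is already intended, one sentence saying so is enough. Say which contrasts the post hoc comparisons are.

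For connectivity, base the efficacy inference on the between-arm comparison of T1-T0 change and report within-condition results descriptively.

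The cost is wording only, using data already planned. The article reports that recruitment had not begun when it was written; if no outcome data have yet been seen, the change can still be prespecified.

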#### Primary Outcomes

##### Pain Intensity (Numeric Rating Scale)

The Numerical Pain Rating Scale [37,38] is an 11-point scale used to measure pain intensity, ranging from 0 (“No pain”) to 10 (“Worst imaginable pain”). It assesses pain through 3 ratings: current pain, highest pain in the last 24 hours, and lowest pain in the last 24 hours, which are then averaged to provide a single score of pain intensity.

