##### Pain Impact (Pain Disability Index)

 The pain disability index [39] is an 11-point scale (0=“no disability”; 10=“worst disability”), a widely used scale that measures pain disability in 7 daily life domains. Higher scores indicate higher pain disability.

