##### Psychological Distress (Depression, Anxiety, and Stress Scale)

 The Depression, Anxiety, and Stress Scale (DASS-21) [39,40] is a 21-item questionnaire composed of 3 subscales designed to measure the negative emotional states of depression, anxiety, and stress. Each of the 3 DASS subscales comprises seven items, which respondents rate on a 4-point severity/frequency scale (0 to 3) in relation to the extent to which they experienced each state over the past week.

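### The reliable change index is used to assess clinically significant individual change, but it shows only that a change exceeds measurement error

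*Protocol article*

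**What the plan says.** The section Data Analyses: Feasibility and Preliminary Efficacy states that "The preliminary efficacy of VR-ACT will be pilot tested through 2 statistical methods". The first is an intention-to-treat linear mixed model of change over time moderated by allocation. The second is the "reliable change index for each outcome for preintervention to postintervention timepoints, to assess clinically significant individual changes", with a literature reference that is not shown.

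The sentence names no second criterion, such as a clinical cut-off, a minimal important change or an anchor. The instrument descriptions do not supply one either:

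- The pain intensity entry gives three 0–10 ratings, "which are then averaged to provide a single score of pain intensity".
- The Pain Disability Index entry gives the direction of scoring: "Higher scores indicate higher pain disability".
- The distress scale entry gives its structure: "Each of the 3 DASS subscales comprises seven items".

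The listed outcomes also include triple-network connectivity, which the same section assigns to network-based statistics, and the System Usability Scale, which it uses to rate VR-ACT itself.

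**The concern.** The index asks whether a person's change is larger than measurement error would readily produce. Clinical significance asks whether the change matters to the patient, or moves the patient into a better clinical range. A change can pass the first test and fail the second, or the reverse. On a precise scale a small change passes. On a noisy scale an important change may not.

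The text ties the clinical label directly to the index, in one of only two named efficacy methods. Followed as written, it would produce counts of participants with clinically significant change that the method cannot support. The Discussion says the results will be a point of reference for a larger multicentre study, so the label should mean what it says.

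**Working it through.** The plan gives no threshold, reliability, SD or count for this analysis, so there is no figure to reproduce. The check is on what the index can measure.

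**Inputs**

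- From the protocol article: the pain score runs from 0 to 10, and the index is applied to each outcome from pre to post.
- Assumed, because the article does not give them: reliability r from 0.70 to 0.95, and pain-score SD from 1.5 to 2.5.

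**Step 1. Threshold.** The standard error of measurement is SD × √(1 − r). The standard error of a difference between two scores is SD × √(2(1 − r)). The two-sided 5% threshold is therefore 1.96 × SD × √(2(1 − r)). SD and r are its only inputs.

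**Step 2. Pain score at SD = 2.**

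- r = 0.9: 1.96 × 2 × √0.2 = 1.75 points
- r = 0.8: 1.96 × 2 × √0.4 = 2.48 points
- r = 0.7: 1.96 × 2 × √0.6 = 3.04 points

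**Step 3. Wider range.**

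| r | Threshold in SD units | Points at SD 1.5 | Points at SD 2.5 |
|---|---|---|---|
| 0.70 | 1.52 | 2.28 | 3.80 |
| 0.80 | 1.24 | 1.86 | 3.10 |
| 0.90 | 0.88 | 1.31 | 2.19 |
| 0.95 | 0.62 | 0.93 | 1.55 |

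The pain change needed for the label runs from about 0.9 to 3.8 points. In SD units, a scale with r = 0.70 needs √(0.30/0.05) = 2.4 times the change that a scale with r = 0.95 needs.

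**Step 4. Direction of error.** Let D be the important change on a scale. If the threshold lies below D, changes between the two are over-labelled. If it lies above D, important changes are missed. For any D between 1.75 and 3.04 points on the pain score at SD 2, either error can occur, depending on r. The article gives no D, so the direction is not fixed.

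**Step 5. Illustration with a cut-off added.** A simulation of 1,000,000 draws assumed a mean true improvement of 0.8 SD, with an SD of change of 0.5. It set a normative mean 1.5, 2 or 3 SD from the patient mean, with the cut-off midway. The stricter rule required the index to be passed and the cut-off to be crossed from the patient side.

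| r | Index alone | Index plus cut-off | Share passing the index but failing the added rule |
|---|---|---|---|
| 0.70 | 22% | 11–15% | 30–48% |
| 0.80 | 29% | 13–18% | 39–55% |
| 0.90 | 45% | 16–23% | 50–65% |
| 0.95 | 62% | 18–26% | 58–71% |

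The last column includes people who were already beyond the cut-off at baseline and so could not cross it. The sizes depend on the assumptions. It is certain only that adding a criterion cannot raise the count.

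**Step 6. Scope of each outcome.** Of the nine outcome headings, seven are self-report scales suited to a pre-post index: pain intensity, disability, distress, quality of life, psychological flexibility, emotion regulation and mindful awareness. Connectivity has its own named method. The usability scale rates a system that participants have not used before the intervention, so it has no meaningful baseline.

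**The case against.** The article does not say that the index is the only criterion. It cites a reference for the procedure in one clause of a condensed report, and that reference or an analysis plan may add a cut-off. Reliabilities, SDs and classification rules per scale are commonly left to such documents, so their absence is no fault. This stands, and it lowers the weight of the point. It does not remove it, because the published sentence itself gives the index the purpose "to assess clinically significant individual changes".

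Four stronger readings are tempting and are not supported:

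- **That responders will be misclassified.** The protocol defines no responder endpoint, and without an important-change value actual mislabelling cannot be shown.
- **That the individual analysis is uncontrolled**, so that regression to the mean or placebo response is credited to the programme. The article is silent on how the index will be compared. The trial is sham-controlled, and its efficacy hypothesis is stated against the sham. Silence does not show that no comparison will be made.
- **That reliability alone sets the threshold.** The SD enters the formula too.
- **That many participants will show a false improvement somewhere.** With no true change and 2.5% flagged per scale, seven independent scales give 1 − 0.975⁷ = 16% with at least one. Correlated scales would probably give less. That figure concerns multiplicity and does not measure the confusion between reliable and important change.

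It is also fair that the index supplements the mixed models in a pilot whose limitations section already cautions against definitive efficacy conclusions. The article ties no progression rule to it.

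**Conclusion.** The point holds as a correction of what the analysis may be said to show. The text presents reliable change as the assessment of clinical significance, and the formula contains nothing that could establish it.

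The figure of about 1.8 to 3.0 points on the pain score rests on an assumed SD of 2 and assumed reliabilities of 0.9 to 0.7. The conclusion does not depend on those values, because clinical importance is missing from the formula whatever they are. The simulated shares are illustrative only.

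The weight is minor to moderate: a supporting analysis in a pilot, with no effect on the mixed models or on N = 30.

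**What to change.** - Report the index result as *reliable change*, split into improved and worsened.
- Use *clinically significant* only for a participant who shows reliable change and also meets a published cut-off or minimal important change, named for that instrument before the data are analysed. Where no such value exists for a scale, report reliable change only.
- Replace *each outcome* with the pre-post self-report scales. Leave connectivity to network-based statistics and the usability scale to the feasibility assessment.
- Report the proportions improved and worsened by arm, with the between-arm difference and its 95% CI. With 15 per arm these intervals will be wide, which suits a pilot.

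The cost is a change of analysis wording and the choice of one criterion per scale. No new data are needed. Some participants will no longer count as clinically improved.

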### Ethical Considerations

All procedures will be conducted in accordance with the 1964 Helsinki Declaration and its subsequent amendments or comparable ethical standards. This study was approved by the Ethics Committee of the Faculty of Psychology and Educational Sciences at the University of Coimbra (ref: CEDI/FPCEUC: 98/R-1). The study will be conducted in accordance with European directives for research involving human participants, such as the General Data Protection Regulation. All participants will provide informed consent to participate in the study. Participants will be provided a patient information sheet with the following information: (1) the aim of the study and the eligibility criteria for participating; (2) the different phases of the study, including assessments and the randomization; (3) the benefits and risks of participating (namely that “We do not anticipate any risks arising from your participation in the study. However, if participating in the study results in a negative emotional experience and you need support, please contact the research team” and other national health resources will be provided). In this case, their participation will be interrupted. (4) Participation is voluntary, participants have the right to drop out without being obligated to provide justification, and access to treatment as usual, as well as their relationships with the medical and nursing team, will not be influenced by this decision; also, the decision to participate will not interfere with their medical treatment; (5) the confidentiality of data will be ensured in all results dissemination activities, and identifiable data in datasets will be password protected, to which only the research team will have access; (6) audio recording of postintervention interviews will be immediately deleted after written transcription. Informed consent will be obtained from each participant by the medical/nursing collaborator who will invite patients to participate before any data collection. (7) The current study will not conduct an assessment of neurological pathology; thus, data collected through fMRI will not be indicative of clinical diagnoses nor associated pathophysiology. The study results will be provided to interested participants in a format that is accessible.

A steering committee composed of 1 participant, 1 physician (anesthesiologist), 1 clinical psychologist, and 1 ethicist will monitor the delivery of the 8-week VR-ACT intervention and ensure the ethical and scientific integrity of the study (eg, adherence to the protocol). The steering committee will gather online at weeks 1, 3, 6, and 8 to discuss the trial progress, methodological issues arising from the implementation, and ethical decision-making. The trial will be interrupted if >50% of participants in the VR-ACT condition report increased psychological distress after session 1, and/or if >50% of the members of the steering committee decide so.

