### Participants

#### Eligibility Assessment

 The study will be conducted in adults diagnosed with CPSP who attend the Neurology Service, Pain Unit, and/or the Rehabilitation Service at the ULS-Coimbra, Portugal. Inclusion criteria include (1) medical diagnosis of CPSP conducted by a medical doctor collaborating with the research team, (2) age between 18 and 80 years, (3) implicit de facto internet and computer literacy, and (4) willingness to comply with the study procedures. Exclusion criteria include (1) currently with active malignancy, (2) severe cognitive impairment, (3) currently undergoing any psychological intervention or VR-delivered pain management program, (4) current severe psychiatric symptoms (ie, psychosis, severe depression, nonsuicidal self-injury, suicide attempt in the last month), (5) language impairment with severe comprehension deficit, (6) history of photosensitive epilepsy or previous experience of severe simulator sickness, and (7) other neurological conditions (eg, dementia or Parkinson disease).

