##### Assessment of the VR-ACT Delivery

The feasibility of the VR-ACT implementation will be evaluated in terms of (1) *adherence*: (a) percentage of participants who completed the intervention, (b) number of sessions completed, and (c) an open-ended question asking the reasons for not completing the intervention; (2) *engagement*: (a) percentage of participants who completed homework assignments and frequency of skills practice between sessions and (b) participants’ average number of VR-ACT device log-ins; (3) *retention/attrition*: number of participants who completed the postintervention assessment; (4) *acceptability*: participants will use a Likert-like scale (eg, 0=not at all; 4=very useful) to rate the VR-ACT modules in terms of its *usefulness*, *comprehensibility*, and *likelihood to continue using learned skills*. Participants will provide suggestions to improve the content of sessions via open-ended questions (see Section A in Multimedia Appendix 1).

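### The no-risk sentence in the information sheet conflicts with the headset hazards recognised in exclusion criterion 6, and no listed feasibility item counts a physical reaction to VR

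*Protocol article*

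**What the plan says.** **Consent wording (Ethical Considerations).** The article reproduces the risk statement from the patient information sheet: "We do not anticipate any risks arising from your participation in the study". The one qualification is that "if participating in the study results in a negative emotional experience and you need support, please contact the research team"; participation is then interrupted. The same section says that the sheet also gives the eligibility criteria.

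**Eligibility (Eligibility Assessment).** Exclusion criterion 6 is "history of photosensitive epilepsy or previous experience of severe simulator sickness".

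**Feasibility and acceptability (Assessment of the VR-ACT Delivery).** The domains are adherence, engagement, retention and acceptability. For acceptability, participants are asked "to rate the VR-ACT modules in terms of its *usefulness*, *comprehensibility*, and *likelihood to continue using learned skills". Adherence includes "an open-ended question asking the reasons for not completing the intervention", and participants may also suggest improvements to session content.

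**Analysis (Data Analyses: Feasibility and Preliminary Efficacy).** The article says that "feasibility will be quantitatively assessed through (1) dropout rate, (2) number of usage of the VR headset", followed by percentage completion and the Likert ratings. Usability is measured by the System Usability Scale. One of the two example interview questions is "What would you say were the benefits of using the VR-ACT headset"; the other asks what was learned.

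**Psychological harm.** The DASS-21 is a primary outcome, and a reliable change index is planned for every outcome. A steering committee meets at weeks 1, 3, 6 and 8. One trigger for interrupting the trial is increased psychological distress after session 1 in more than half of the VR-ACT arm; a committee majority can also interrupt it.

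**The concern.** There are two linked problems.

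The first is consent. An exclusion for photosensitive epilepsy or severe simulator sickness makes sense only if the headset is thought able to provoke such reactions. A participant who is told that no risks are expected, with emotional discomfort as the sole caveat, is told less than the eligibility criteria imply.

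The second is measurement. The listed indicators of success ask whether people finished, logged in, returned the questionnaires, found the modules useful and clear, and found the system easy to use. Someone who feels sick in every module but completes them all counts as adherent and retained, and no listed item would show the sickness. The trial is meant to support a conclusion of feasibility and acceptability and to prepare a larger multicentre study. On the listed items, that conclusion could be reached with physical tolerability uncounted. The post-intervention interview, where a reaction might be mentioned, is held in the experimental arm only, so it offers no comparison with the sham arm.

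**Working it through.** **Step 1: the consent sentence beside the exclusion criterion.** The article states no figure to reproduce here, so this is a comparison of text.

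- Information sheet: no risk anticipated; emotional experience is the only harm named.
- Exclusion criterion 6: two physical hazards, each screened by the person's history.

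Does screening by history remove the hazards from the eligible group? For simulator sickness it does not. The criterion requires a previous severe episode, and a person who has never used such equipment cannot have had one. For photosensitive epilepsy, the criterion works without any headset exposure, because the condition may already be known. It still depends on a known history. The hazards are reduced, and the statement that none is anticipated goes further than the criterion supports.

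**Step 2: each listed measure against physical reactions.**

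| Item in the article | Counts a physical VR reaction? |
|---|---|
| Adherence: completion, sessions completed | No |
| Reasons for not completing (open question) | Only if volunteered, and from non-completers only |
| Engagement: homework, skills practice, log-ins | No |
| Retention: post-intervention assessment completed | No |
| Acceptability: usefulness, comprehensibility, continued use | No |
| Suggestions to improve content (open question) | Only if volunteered |
| System Usability Scale | No; described as a global view of usability |
| Registration system: complete and incomplete sessions | Shows that a session stopped, not why |
| Two phone calls; contact details at the start of each module | Only if volunteered; the stated purposes are content questions and technical problems |
| DASS-21 with reliable change index | Psychological change only |
| Distress trigger after session 1 | Psychological distress only |

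Several routes could bring a reaction to light. None of those listed counts reactions systematically.

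**Step 3: what a count in this trial could show.** The arm size is 15 (Sample Size Calculation). The article gives no rate of simulator sickness, so the rates below are assumptions.

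Chance of at least one affected person among 15 = 1 − (1 − p)^15:

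- p = 1%: 1 − 0.99^15 = 0.140
- p = 5%: 1 − 0.95^15 = 0.537
- p = 10%: 1 − 0.90^15 = 0.794
- p = 20%: 1 − 0.80^15 = 0.965

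Exact 95% upper bound when 0 of 15 are affected:

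- one-sided: 1 − 0.05^(1/15) = 0.181
- two-sided: 1 − 0.025^(1/15) = 0.218

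A common reaction would probably appear at least once and could be described. A rare one, such as a seizure, would probably not appear, and its absence would say little.

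**The case against.** The strongest reply has four parts.

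1. *Harm is already monitored.* A reader might infer from the points above that the trial has no measure of harm. The article does not support that. The DASS-21 with a reliable change index can show individual psychological deterioration in both arms, pain intensity and disability can be seen to worsen, and a steering committee that includes a physician can interrupt the trial. This part stands, and it limits the measurement point to physical reactions.

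2. *The two statements are compatible.* Criterion 6 removes susceptible people, and the sheet speaks to those who remain. The sheet also lists the eligibility criteria, so participants should see the exclusion. This stands far enough that the passages are better called conflicting than strictly contradictory. It does not rescue the sentence, because a history-based exclusion leaves first-time users at unknown risk. Printing the exclusion in the same sheet as a no-risk statement also leaves the participant to reconcile the two.

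3. *Recording may be described elsewhere.* The text is a condensed article. The SPIRIT figure, Multimedia Appendix 1 with the interview guide, and the full protocol are not shown, and the interview questions quoted are examples only. This stands. It would be wrong to conclude that nothing in the plan records physical reactions; the point holds only for the items that the article lists. It does not touch the consent wording, because both statements are printed in the article.

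4. *The assumed rates prove little.* They show that an event could occur, not that a planned conclusion would change. This is fair. They are illustrative, and the consent point does not depend on them.

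**Conclusion.** The concern holds in limited form and should be addressed. The no-risk sentence fits poorly with the hazards that exclusion criterion 6 recognises, and this rests on printed text alone. Separately, none of the feasibility, acceptability or usability items in the article counts a physical reaction to the headset. On those items, a favourable conclusion could be drawn without one. That second part assumes that the material not shown contains no such recording.

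Its practical size depends on an unknown rate: at assumed rates of 5% to 20%, the chance of at least one affected person among 15 VR-ACT users is 54% to 96%. Counting would not allow this trial to establish the absence of risk, since zero events in 15 is compatible with a true rate of up to about 18% (one-sided 95%). The gain is an accurate consent statement and a descriptive account of tolerability for planning the larger study.

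**What to change.** 1. Reconcile Ethical Considerations with Eligibility Assessment, so that the information sheet states the risks that the exclusion criteria already recognise.

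2. State where physical reactions are recorded. If they are not recorded anywhere, have the registration system show the same short prompt at the end of every module in both arms: simulator-sickness symptoms, any other physical reaction, and whether the session was stopped early because of symptoms.

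3. Add the number and proportion of participants affected in each arm, with exact confidence intervals, to the feasibility outcomes. Report them beside any conclusion on acceptability and label them descriptive.

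**Cost.** An ethics amendment to the sheet, a few screen items in software that the article describes as still to be developed, and about one minute per weekly module. Prompting may slightly raise symptom reporting; using the same prompt in both arms should keep the comparison fair. The article says that recruitment had not started, so these changes fit best before the first participant consents.
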